**Fig. 1 Fig1:**
[figure not shown]
Flow diagram of trial progression

### Intervention

Silence is Deadly is a face-to-face multicomponent intervention targeted to males in secondary schools (12–18 years) in the ACT. The program is delivered to students over a 45–60 min group session by a facilitator, with traditional male role models (e.g., rugby players, military personnel). Program facilitators play a central role in the program, speaking about their own positive help-seeking experiences in response to personal difficulties, and the lessons they have learnt in countering traditional masculine norms. Professional athletes are another important element in the intervention, acting as role models in the delivery of the program and/or being included in a video that counters existing male norms that prevent positive help-seeking attitudes, and promote the importance of communicating about personal issues. All discussions are tailored to the male audience and include seeking support for mental health issues resulting from bullying, injuries, relationship issues and other circumstantial stressors, as well as how to ‘help a mate’ (i.e., start a conversation with a friend) who is not doing well. The program concludes with a question and answer session that lasts 5 to 15 min. The purpose of the intervention is to normalise the occurrence of mental health issues in young men and alter their attitudes to help-seeking by reframing them in the context of broader help-seeking norms for personal problems, which are less stigmatising and more compatible with typical gender roles.

### Assessments

Table 1 presents the scales that will be administered at each measurement occasion in the Silence is Deadly trial. With the exception of the Confidence Supporting Peers scale (see below), all measures have previously been evaluated with adolescent samples and have good psychometric properties.

**Table 1 Tab1:** Measures for the silence is deadly trial

	Pre-intervention	Post-intervention	3-month follow-up	No. of items
Demographics	✔	✔	✔	7
Adapted GHSQ	✔	✔	✔	20
Adapted AHSQ	✔	✔	✔	22
Help-seeking from adults	✔	✔	✔	4
ATSPPH-SF	✔	✔	✔	10
SSOSH	✔	✔	✔	10
Confidence in supporting a friend	✔	✔	✔	4
DQ5	✔	✔	✔	5
YRBS	✔	✔	✔	1
GRCS-A	✔			9
Program evaluation^a^		✔		4

*Notes. AHSQ* Actual Help-Seeking Questionnaire, *ATSPPH-SF* Attitudes Toward Seeking Professional Psychological Help Scale - Short Form, *DQ5* Distress Questionnaire-5, *GHSQ* General Help-Seeking Questionnaire, *GRCS-A* Gender Role Conflict Scale—Adolescent Version, *SSOSH* Self-Stigma of Seeking Help Scale, *YRBS* Youth Risk Behaviour Survey

^a^Only students in intervention schools respond to these questions

#### Help-seeking intentions

An adapted version of the General Help-Seeking Questionnaire (GHSQ) [24] will be used in the current study to assess the primary outcome of help-seeking intentions for personal or emotional problems from 11 different formal and informal sources (e.g., friend, parent, psychologist, or teacher). Respondents indicate how likely they are to seek help from each of the sources on a scale ranging from 1 (extremely unlikely) to 7 (extremely likely). The wording of questions was adapted from ‘seeking help’ to ‘seeking advice’ to reflect the language used in the Silence is Deadly program.

#### Attitudes to seeking support from trusted adults

The 4-item Attitudes to Seeking Support from Trusted Adults scale will be used in the current study to assess help-seeking attitudes. Respondents indicate their agreement with items on a 4-point scale ranging from 1 (strongly disagree) to 4 (strongly agree). The scale is drawn from a US trial of the Sources of Strength suicide prevention program [25]. This scale also assesses respondents’ view of their family and friends’ norms regarding seeking help and support from trusted adults. Total scale scores on this scale can range from 4 to 16, with higher scores indicative of more positive help-seeking attitudes.

#### Attitudes to help-seeking from professionals

The Attitudes Toward Seeking Psychological Professional Help: Shortened Form (ATSPPH-SF) [26, 27] will be also be used to measure help-seeking attitudes. This scale aims to assess respondents’ attitudes towards self-reliance and professional support for personal and emotional problems. The ATSPPH-SF consists of 10 items: responses are on a 4-point scale ranging from 0 (disagree) to 3 (agree). Some items are negatively-worded to address positive response bias. After reverse-scoring of these items, total scale scores can range from 0 to 30, with higher scores reflecting more positive attitudes towards seeking help from professionals.

#### Help-seeking Behaviours

The adapted Actual Help-Seeking Questionnaire (AHSQ) [24], will be used to assess recent actual help-seeking behaviour for personal or emotional problems and assesses the same 11 sources of help as the GHSQ. Respondents are asked whether or not they have sought help for personal or emotional problems from 11 different formal and informal sources (e.g., friend, parent, psychologist, or teacher) in the past 3 months. The question wording was adapted from ‘seeking help’ to ‘seeking advice’ to reflect the language used in the Silence is Deadly program.

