#### Secondary aims

The secondary aims of the trial are:To test the effectiveness of the Silence is Deadly program in (a) increasing actual help-seeking behaviour, (b) improving help-seeking attitudes, and (c) reducing help-seeking stigma at post-intervention and 3-month follow-up.To investigate the extent to which the effect of the intervention is mediated or moderated by the attitudinal characteristics of participants, including gender role conflict and help-seeking stigma. This aim is driven by the program’s intention to be effective for males who conform strongly to gender role norms, such as emotion suppression, and who hold more stigmatising attitudes towards seeking help for emotional problems.To explore (a) if there is a differential effect of the intervention based on pre-intervention levels of psychological distress or suicidal ideation, and (b) the impact of the program on self-reported psychological distress and suicidal ideation at post-intervention and 3-month follow-up.To explore the impact of the intervention on (a) student confidence to provide support to their peers at post-intervention and 3-month follow-up, and (b) school culture towards seeking help for emotional and/or personal problems. The latter aim will be investigated through semi-structured interviews with key staff members.

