#### Trial hypotheses

H1: The Silence is Deadly program will improve participants’ intentions to seek help for personal and emotional problems at post-intervention and 3-month follow-up, regardless of indicated levels of mental health symptoms or suicidality, relative to participants in the wait-list control condition.H2: The Silence is Deadly program will increase participants’ rates of informal and formal help-seeking for personal and emotional problems at 3-month follow-up relative to participants in the wait-list control condition.H3: The Silence is Deadly program will improve participants’ help-seeking attitudes and reduce help-seeking stigma at post-intervention and 3-month follow-up relative to participants in the wait-list control condition.H4: The Silence is Deadly program will be significantly more effective among participants who hold strong masculine role norms or higher help-seeking stigma at pre-intervention.

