## Methods/design

### Study design

A two-arm cluster randomised controlled trial (RCT) will be conducted with one active intervention group and one wait-list control group. Surveys will be delivered on three measurement occasions - one-week pre-intervention, one-week post-intervention and at approximately 3-months follow-up. A qualitative evaluation of the intervention will also be conducted, comprising semi-structured interviews with selected staff members from all participating schools.

The ethical aspects of this study have been approved by The Australian National University Human Research Ethics Committee (protocol number 2017/004), Catholic Education Office of the Archdiocese of Canberra and Goulburn, and the ACT Education Directorate (reference RES-1719).

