Following completion of the pre-intervention survey, students in intervention condition schools will receive the Silence is Deadly intervention during school hours. Students in control condition schools will undertake usual school activities during this period. Approximately 2 weeks after the pre-intervention survey, students in both intervention and control condition schools will complete the post-intervention survey. A final 3-month follow-up survey will also be administered to all students, after which time schools in the wait-list control condition will receive the Silence is Deadly program. Figure 1 presents the flow of participants in the trial (See Additional file 1: Attachment A for SPIRIT Checklist). Semi-structured interviews will also be conducted with selected staff members in all schools to qualitatively assess cultural changes in the school and attitudinal changes in students, associated with the Silence is Deadly program.

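### The post-intervention survey asks about help-seeking over 3 months, about 12 of 13 weeks of which precede the program, yet secondary aim 1(a) tests behaviour there while H2 names only 3-month follow-up

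*Protocol article*

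**What the plan says.** **Recall and response.** Under Help-seeking Behaviours, the adapted AHSQ is a yes/no measure. Its sources and recall period are given as "from 11 different formal and informal sources (e.g., friend, parent, psychologist, or teacher) in the past 3 months". No other recall period is given. Table 1 ticks its 22 items at pre-intervention, post-intervention and 3-month follow-up.

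**Timing.** Study design places the surveys "one-week pre-intervention, one-week post-intervention and at approximately 3-months follow-up". Procedure agrees: "Approximately 2 weeks after the pre-intervention survey, students in both intervention and control condition schools will complete the post-intervention survey".

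**Aim and hypotheses.** The first of the Secondary aims covers "a) increasing actual help-seeking behaviour, (b) improving help-seeking attitudes, and (c) reducing help-seeking stigma at post-intervention and 3-month follow-up". In Trial hypotheses, H2 concerns "rates of informal and formal help-seeking for personal and emotional problems at 3-month follow-up" and does not mention post-intervention. H3, on attitudes and stigma, names both occasions.

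**Analysis.** Statistical analysis assigns binary outcomes to binary mixed models built like the linear repeated-measures model. It makes no exception for the AHSQ at any occasion.

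**The concern.** A measure can show a program effect only through the part of its recall period that follows the program. At the post-intervention survey that part is about one week in 13. The remainder is behaviour that the program could not have influenced, and most of it was already reported at the pre-intervention survey.

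If behaviour is nonetheless a declared effectiveness test at that occasion, a difference near zero is the expected result even when the program works. Readers may then take it as a finding about the program when it mainly reflects the recall period. Because the aim and H2 name different occasions, it is also not settled which behaviour result counts. That should be fixed before results are seen.

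**Working it through.** The plan states no expected AHSQ rate or AHSQ power, so there is no figure to reproduce. The first step uses only the plan's own timings. The second and third rest on stated assumptions.

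**Step 1: the recall window at the post-intervention survey.** Inputs: recall W = 3 months, about 13 weeks (Help-seeking Behaviours); 1 week since the program (Study design); 2 weeks since the pre-intervention survey (Procedure).

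- Share before the program = (W − 1)/W = 12/13 = 92.3%; share after = 1/13 = 7.7%.
- Overlap with the pre-intervention window = (W − 2)/W = 11/13 = 84.6%.
- With 3 months taken as 12 weeks: 11/12 = 91.7% before, 1/12 = 8.3% after, overlap 10/12 = 83.3%.

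At 3-month follow-up the same recall lies almost wholly after the program.

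**Step 2: dilution.** Assumptions, not in the documents: a constant weekly rate of help-seeking; a share p0 of controls answering yes over 13 weeks; a weekly rate multiplied by RR from the program onwards. Let H = −ln(1 − p0).

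- Post-intervention: p = 1 − exp(−H × (12 + RR)/13)
- 3 months: p = 1 − exp(−H × RR)

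For p0 = 30% and RR = 2, H = 0.3567. Post-intervention: 1 − exp(−0.3567 × 14/13) = 1 − exp(−0.3841) = 31.9%. At 3 months: 1 − exp(−0.7133) = 51.0%.

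| Control rate | RR | Post-intervention (difference) | 3 months (difference) |
|---|---|---|---|
| 20% | 1.5 | 20.7% (0.7 points) | 28.4% (8.4 points) |
| 20% | 2 | 21.4% (1.4) | 36.0% (16.0) |
| 30% | 1.5 | 31.0% (1.0) | 41.4% (11.4) |
| 30% | 2 | 31.9% (1.9) | 51.0% (21.0) |
| 50% | 1.5 | 51.3% (1.3) | 64.6% (14.6) |
| 50% | 2 | 52.6% (2.6) | 75.0% (25.0) |

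**Step 3: what this means for detection.** From Sample size and power calculations: 800 students in 8 schools, 20% attrition, intra-class correlation 0.03. That leaves 640 students, 80 per school and 320 per arm. The design effect is 1 + 79 × 0.03 = 3.37, so the effective number per arm is 320/3.37 = 95. Power for two proportions (normal approximation, two-sided 5% level assumed, rejections in the right direction only) is Φ((difference − 1.96 × SE0)/SE1), where SE0 and SE1 are the standard errors with pooled and separate variances.

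- RR = 2, post-intervention: about 4% to 6% for control rates of 20% to 50%. With no effect at all the figure would be 2.5%.
- RR = 2, 3 months: about 69% to 95%.
- RR = 5, post-intervention: about 14% to 26%.

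These figures make no baseline adjustment and no allowance for having only 8 schools, and they borrow an intra-class correlation not stated for the AHSQ. They serve only to compare the two occasions.

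**Step 4: aim against hypothesis.** The closing time points of aim 1 read most naturally as covering (a), (b) and (c): H3 gives (b) and (c) those same time points, and Table 1 schedules the AHSQ at post-intervention. H2 names 3 months only. The two statements of when behaviour is tested therefore do not match.

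**The case against.** **The mismatch may be only loose wording.** The time points in aim 1 could be attached to (c) alone, and H2, the narrower statement, already uses the suitable occasion. The contrast with H3 suggests this was deliberate. That is fair, and it makes this a mismatch of time points in a secondary aim, not a flat contradiction. It does not remove the point: the natural reading of the aim still makes post-intervention behaviour an effectiveness test, and nothing in the article excludes it.

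**A short-term effect is not impossible.** A reader might infer that the post-intervention comparison cannot show an effect. The documents do not support that. Step 2 gives small but non-zero differences, and an early burst of help-seeking is conceivable, since Procedure offers priority counselling appointments. A fivefold rate would give 37.3% against 30%. The measure is heavily diluted, not null by construction.

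**Power at 3 months.** A reader might also infer that the post-intervention wave costs power for the 3-month comparison, for example 80% falling to 71%, or 85% to 77%. That requires a joint two-degree-of-freedom test of time by condition, which Statistical analysis does not specify; the model also yields a contrast at each occasion. It further requires the two change-from-baseline contrasts to be uncorrelated, although they share a baseline. With contrast correlation r and an effect only at 3 months, the joint non-centrality is the single-contrast value divided by (1 − r²). With the plan's repeated-measures correlation of 0.5 between all waves, r = 0.5 and 7.85 becomes 7.85/0.75 = 10.47. Joint power is then about 83% instead of 80%, and likewise 88% instead of 85%. If the overlapping windows raise the pre-post correlation to 0.85 (assumed), r = 0.27 and the figures are 74% and 80%. No power loss can be asserted from this plan.

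**The wave has some use.** With 20% attrition and a model assuming data missing at random, an intermediate wave can inform estimates for students absent at 3 months. This stands, and it favours keeping the wave as descriptive over dropping it.

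**Conclusion.** The point holds as a modest one about a secondary outcome; the primary outcome, help-seeking intentions, is unaffected. On the plan's own schedule, about 92% of the AHSQ recall at post-intervention precedes the program and about 85% repeats the pre-intervention window. This needs no outside figure. Under assumed control rates of 20% to 50% and a doubled weekly rate, the expected difference is 1.4 to 2.6 percentage points at post-intervention against 16 to 25 at 3 months. The size of the dilution rests on the constant-rate assumption; its direction does not. A null result at post-intervention would say very little about whether the program changes behaviour. The recall suits the 3-month test, and H2 is sound as written.

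**What to change.** Amend secondary aim 1(a) to match H2, so that the effectiveness test of help-seeking behaviour is the 3-month contrast from the planned binary mixed model. No change of model is needed. For the post-intervention survey, choose one of:

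- keep the AHSQ there and label it descriptive only;
- keep it as a short-term measure, but ask about the time since the last survey, and report it descriptively;
- drop it from that column of Table 1, which shortens the survey by 22 items.

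The costs are small. There is no confirmatory short-term result for behaviour. Rewording makes the recall period differ between waves, and dropping the wave loses a little information on students missing at 3 months. Trial status says recruitment is under way, so the change should be made and dated before any results are seen. If some schools have already completed the post-intervention survey, the first option is the simplest because it leaves the questionnaire unchanged.

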#### Stigma of help-seeking

The Self-Stigma of Seeking Help Scale (SSOSH) [28] will be used in the current trial to assess the extent to which respondents hold stigmatised attitudes towards seeking or receiving support for their own personal or emotional problems. Attitudes are measured by 10 items on a 5-point scale ranging from 1 (strongly disagree) to 5 (strongly agree). Some items are negatively-worded to address positive response bias. After reverse-scoring of these items, total scale can range from 10 to 50, with higher scores reflecting more self-stigma towards seeking help.

#### Mental health symptoms

General psychological distress will be assessed with the Distress Questionnaire Scale – 5 (DQ5) [29]. This scale consists of 5 items rated on a 5-point scale from 1 (never) to 5 (always), with total scale scores ranging from 5 to 25. Higher scores on the DQ-5 reflect greater psychological distress.

#### Suicidality

One item from the Youth Risk Behaviour Survey (YRBS) [30, 31] will be administered to assess if the respondent has had suicidal ideation during the past 12 months (response options: yes or no). Research indicates that the measurement of suicidal behaviours in adolescents is acceptable and does not pose an iatrogenic risk [32].

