**Methods:**

This study is a two-arm, cluster-randomised, controlled trial that will compare the Silence is Deadly program to a wait-list control condition. Eight Australian high schools will be recruited to the trial, with male students in grades 11 and 12 (16 to 18 years of age) targeted for participation. The program is an innovative male-tailored suicide prevention intervention, comprising a presentation that emphasises role-modelling and legitimises help-seeking for personal and emotional problems, and a brief video that features celebrity athletes who counter existing male norms around help-seeking and encourage communication about personal and emotional issues. The program also includes a discussion of how to help a friend in distress and ends with a question and answer session. The primary outcome measure for the current study is help-seeking intentions. Secondary outcomes include help-seeking behaviour, help-seeking attitudes, help-seeking stigma, mental health symptoms, and suicidal ideation. Data will be collected pre-intervention, post-intervention, and at 3-month follow-up. Primary analyses will compare changes in help-seeking intentions for the intervention condition relative to the wait-list control condition using mixed-effects repeated-measures analyses that account for clustering within schools.

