### Statistical analysis

Analyses of primary and secondary effectiveness outcomes will be conducted using a mixed-model repeated measures (MMRM) approach [35], the standard and most robust methodology for analysing randomised controlled trials. This approach is able to include participants with missing data without using biased imputation techniques, assuming that data are missing-at-random. Further, by incorporating appropriate random effects for each school, MMRM can accommodate and assess the strength and significance of clustering effects. Identification of moderating factors, such as mental health symptoms, suicide behaviours, stigma and gender-role conflict, will be conducted by introducing three-way interaction terms of time × condition × moderator, also using MMRM. Analysis of binary outcomes will be undertaken using binary mixed models, analogous to linear MMRM.

Qualitative analysis of the semi-structured interviews will be conducted using Framework Analysis. Framework Analysis was designed for addressing social policy research questions [36] and has been used frequently in health research [37]. It follows a systematic process of inductive coding, generating a table of findings across participants that is conducive to interpretation and input from multiple researchers.

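### The only suicidal ideation item looks back 12 months at every survey, so the planned impact contrast is essentially uninformative at one week and strongly diluted at 3 months

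*Protocol article*

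**What the plan says.** The Suicidality section describes one yes/no item from the Youth Risk Behaviour Survey, used "to assess if the respondent has had suicidal ideation during the past 12 months (response options: yes or no"). Table 1 under Assessments ticks that item in all three survey columns, and no other look-back is given for the later surveys. Study design sets the surveys at "one-week pre-intervention, one-week post-intervention and at approximately 3-months follow-up". Procedure agrees: "Approximately 2 weeks after the pre-intervention survey, students in both intervention and control condition schools will complete the post-intervention survey".

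The item has two uses. The third secondary aim makes baseline ideation a possible effect modifier (part a) and also sets out to explore "the impact of the program on self-reported psychological distress and suicidal ideation at post-intervention and 3-month follow-up" (part b). The Abstract counts ideation as an outcome: "Secondary outcomes include help-seeking behaviour, help-seeking attitudes, help-seeking stigma, mental health symptoms, and suicidal ideation". Under Statistical analysis, "Analysis of binary outcomes will be undertaken using binary mixed models, analogous to linear MMRM".

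The behaviour measure is built differently. The Help-seeking Behaviours section asks about help sought "from 11 different formal and informal sources (e.g., friend, parent, psychologist, or teacher) in the past 3 months", a window that matches the 3-month follow-up.

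**The concern.** An outcome can register an intervention only over time that follows the intervention. Here the window is a year and the follow-up is at most about 3 months, so most of what a student reports at either later survey was settled before the program was delivered. Randomisation balances that earlier time between the arms but does not remove it. It adds the same pre-program ideation to both arms and pulls the risk ratio toward 1.

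What is at stake is the reading of the result. The Abstract describes the program as suicide prevention, so readers will look at the ideation contrast. If it shows no difference, the item gives them no way to tell a program without effect from one whose benefit or harm lies outside most of the window.

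**Working it through.** The plan states no figure for this outcome, so there is none to reproduce. The check has four steps.

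**1. Share of the window before the program.** Inputs: a 12-month window (52 weeks, Suicidality); surveys 1 week and about 3 months after the program (Study design, taken as 13 weeks).

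Share before = 1 − (weeks since the program)/52.

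- One-week survey: 51/52 = 98%.
- 3-month survey: 39/52 = 75%. If the 3 months run from the post-intervention survey (14 weeks), 38/52 = 73%.

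Overlap with the window already asked about at baseline, using the 2-week gap in Procedure: 50/52 = 96% at the one-week survey, and 38/52 to 37/52 = 73% to 71% at 3 months. These shares need only the stated window and dates.

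**2. Dilution with independent episodes.** The article gives no prevalence. I assume a 12-month prevalence p of 10% to 20%, a constant rate and accurate recall. With H = −ln(1 − p), w weeks since the program and a true rate ratio R from the day of delivery:

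P(yes, intervention arm) = 1 − exp(−H × [(52 − w)/52 + R × w/52]); P(yes, control arm) = p.

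Worked case: p = 0.15, H = 0.1625, R = 0.5, w = 13. The bracket is 0.75 + 0.125 = 0.875, so P = 1 − exp(−0.1422) = 0.1326, and the observed risk ratio is 0.1326/0.15 = 0.884.

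| True effect | p | Risk ratio at 1 week (difference, points) | Risk ratio at 3 months (difference, points) |
|---|---|---|---|
| Halved (R = 0.5) | 10% | 0.991 (0.09) | 0.881 (1.2) |
| Halved | 15% | 0.991 (0.13) | 0.884 (1.7) |
| Halved | 20% | 0.991 (0.17) | 0.887 (2.3) |
| Abolished (R = 0) | 10% | 0.982 (0.18) | 0.760 (2.4) |
| Abolished | 15% | 0.982 (0.27) | 0.765 (3.5) |
| Abolished | 20% | 0.983 (0.34) | 0.771 (4.6) |

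**3. Dilution if episodes recur in the same students.** Suppose ideation is confined to a vulnerable subgroup with λ episodes a year. The 3-month risk ratio for a true halving is [1 − exp(−0.875λ)]/[1 − exp(−λ)].

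- λ = 2: 0.826/0.865 = 0.956.
- λ = 4: 0.970/0.982 = 0.988.

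**4. The same halving with a 3-month window at follow-up.** No part of the window now precedes the program. With independent episodes the risk ratio is about 0.50 to 0.51. With recurrence it is [1 − exp(−0.125λ)]/[1 − exp(−0.25λ)], which is 0.562 for λ = 2 and 0.622 for λ = 4.

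Illustrative power for a true halving uses the planning figures under Sample size and power calculations. There are 800 students in 8 schools; 20% attrition leaves 320 per arm, 80 per school. With an intra-class correlation of 0.03 the design effect is 1 + 79 × 0.03 = 3.37, so about 95 effective students per arm. Alpha is assumed to be 0.05 two-sided. The normal approximation counts rejections in the correct direction only. Power is about 3% to 6% with the 12-month item and about 9% to 19% with the 3-month window. Eight schools leave few degrees of freedom, so both are optimistic.

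**The case against.** Several points on the other side stand.

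- **The aim is exploratory.** The third secondary aim is framed as exploration, none of H1 to H4 predicts an effect on ideation, and the primary outcome is help-seeking intentions. This limits the weight of the point. Part (b) also covers distress, which has its own scale and no stated 12-month window.
- **The loss is of sensitivity.** The look-back is the same in both randomised arms, so the mismatch does not in itself create a false difference.
- **A standard item keeps its wording, and the full protocol might shorten it.** The second half is speculation. The article reports the wording changes made to the help-seeking intentions and behaviour questionnaires and reports none for this item.
- **A shorter window does not rescue the outcome.** This is correct: on the figures above, power remains below 20% for a halving.

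A reader might also infer more than the documents support. The 3-month contrast is not incapable of showing anything, because a quarter of its window follows the program and complete abolition would appear as a risk ratio of about 0.77. Nor must a student who answers yes at baseline do so at every survey. The window moves, so ideation confined to its earliest 14 or 15 weeks would have dropped out by the 3-month survey. Finally, the article makes no safety claim from this item, and its at-risk procedure rests on screening each survey, not on the comparison of arms.

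**Conclusion.** The point holds as a mismatch between measure, schedule and aim, all three of which the article states. The one-week ideation contrast is essentially uninformative, with 98% of its window before the program. The 3-month contrast is strongly diluted, with 75% before it. Those shares follow from the documents. The risk ratios for a true halving (about 0.99 at one week; 0.88 to 0.89 at 3 months, or 0.96 to 0.99 with recurrence) rest on an assumed prevalence of 10% to 20%, a constant rate, accurate recall and an effect starting on the day of delivery. A null finding could not be read as no impact. The change is worth making because recruitment is still open, but the point concerns an exploratory aim and leaves the primary outcome untouched. The 12-month item remains suitable as a baseline moderator.

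**What to change.** 1. Keep the 12-month item at the pre-intervention survey as the moderator for part (a) of the third secondary aim.
2. Add an ideation item on the past 3 months at baseline and at the 3-month follow-up. A window that runs from the program would also serve at follow-up, but control students have had no program by then, so a calendar window common to both arms is simpler.
3. For part (b), use the follow-up answer to the short item as the outcome in a binary mixed model with a school random effect, adjusted for the baseline short-window answer.
4. Remove the one-week post-intervention ideation contrast from part (b).
5. If the surveys can no longer be changed, use ideation as a moderator only and do not interpret it as an impact outcome.
6. Leave the at-risk screening of surveys as it is.

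Cost: one or two extra items and an ethics amendment, with three approving bodies named under Study design. The reworded item would lack the validation that the Assessments section claims for the existing measures. The analysis of this outcome becomes a baseline-adjusted comparison at one time point in place of a three-wave repeated-measures model. Power stays low with 8 schools, so the result should be reported as exploratory, with its confidence interval.
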